| DESIGN | Through NHS clinical services in colorectal surgery and oncology, patients will be identified and recruited from surgical wards or surgical/oncology out-patient clinics. A sample of participants with and without a new or previous diagnosis of colorectal cancer will be included for comparison.  Participation will consist of two events in the majority of participants. Firstly a in the surgical ward or clinic lasting no longer than 20 minutes in which the research will be discussed and informed consent gained. A blood sample will be taken prior to the conclusion of recruitment and a rectal biopsy taken using a rigid sigmoidoscopy which may or may not be required as part of their routine clinical assessment. Participants will be asked to take pharmaceutical grade vitamin D tablets for 3 months. After 12 weeks of vitamin D supplementation, a final blood sample and rectal biopsy will be taken.  **If patients would like to contribute but cannot or would prefer not to take vitamin D, or cannot return for future sampling, a single sampling will be offered. This participant would undergo blood sampling and rectal biopsy as above. After this no further events would occur.** |
| AIM | To identify the underlying mechanism by which Vitamin D reduces colorectal cancer risk. |
| OBJECTIVES | To demonstrate the effects of vitamin D supplementation on serum vitamin D levels.  To demonstrate dynamic changes in gene expression in response to vitamin D.  To demonstrate the mechanism underlying the gene-environment interaction of vitamin D, susceptibility genetic variants (risk genes) and colorectal cancer. |
| OUTCOME  MEASURES | *Primary outcome:* Change in expression of genes in bowel tissue in response to vitamin D  *Secondary outcomes:*  Change in expression of genes in bowel tissue in response to vitamin D dependent on participant genotype  Change in serum vitamin D level in response to vitamin D supplementation.  Change in tissue vitamin D level in response to vitamin D supplementation. |
| ELIGIBILITY | Aged 16 years or over.  Resident of the UK. |

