# 3. STUDY DESIGN

# 3.1 STUDY OUTCOME MEASURES

PRIMARY OUTCOME – the change in expression of genes relevant to colorectal cancer risk in response to vitamin D supplementation.

SECONDARY OUTCOMES - the genotypic associations with changes in gene expression in response to vitamin D supplementation, the change in serum and tissue vitamin D level after vitamin D supplementation.

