# 5.6 LABORATORY SAMPLES

A blood sample will be taken into 2 lithium heparin tubes and 2 EDTA tubes by venepuncture (~30mls). The rectal biopsy will be taken into RNA preservative. If patients are required to undergo further endoscopy for clinical reasons, we will request a study biopsy to be taken during this. All samples will be anonymised through use of an identifying number and will be processed by the Wellcome Trust Clinical Research Facility (WTCRF), Western General Hospital, Edinburgh. The research team will make arrangements for the safe transport of samples to the WTCRF through the use of a pre-paid sealed transport system. Following 12 weeks of Vitamin D supplementation repeat blood (~30mls) and rectal biopsies will be taken.

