# 5.8 DEMOGRAPHIC DATA

Any documented occurrence of bowel polyps will be recorded along with any pre-operative and / or post-operative treatment including any short or long course of radiotherapy, chemo-radiation, combination chemotherapy, mono-chemotherapy or palliative chemotherapy in participants with colorectal cancer.

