# 7.2 METHODS OF ANALYSIS

Serum vitamin D measurement will be undertaken by Liquid chromatography–mass spectrometry (Glasgow RI Biochemistry). Bowel tissue (rectal biopsy) measurement of vitamin D will be undertaken using a novel assay system reported in the literature (Immunodiagnostic Systems, Scottsdale, AZ, USA).

Genotyping will be undertaken to identify risk alleles using Illumina OmniExpress Exome GWAS arrays which provides comprehensive cost-efficient genotyping of loci of interest and pre and post active treatment gene expression assessed using Illumina HT-12 array and validated using qRT-PCR. Statistical comparison of pre- and post-treatment gene expression will be undertaken using the Mann-Whitney U test.

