# SCoViDS DATA COLLECTION PROFORMA

For completion by researcher

**Name**: ……………………………….…..……………

MD:

**Address**: ………………………….….….……………

**Male / Female** …………………………………………………………

**Ethnicity:**…………………. **DOB**: ………………..………

**Participant involved in any previous genetic studies?** Yes / No / Unsure

**Takes regular aspirin? ** Yes **** No

(or product containing aspirin)

If yes, reason …………. Dose: .mg …………….

**Previous or new diagnosis of colorectal cancer? ** Yes **** No

Date (year) ………………

**Consultant**: …………………………………………

**GP details**: ..…………………………………………………………………………………………….

**New or previous diagnosis of colorectal cancer?** Yes / No

**Date of surgery**: ……..………………… **or** / no surgery planned.

**Is this a 2nd primary colorectal tumour?**  Yes / No

**Is this a recurrence?**  Yes / No

**Pre-op treatment**: No / Short course XRT */ Long course XRT **/ Long course chemoradiation

**Post-op treatment** : No / combination chemo / mono chemo / palliative chemo / radiotherapy/ undetermined

***Definitions:*** ** Short course XRT occurs in the 5 days leading up to the day operation ** Long course is 6 weeks +/- chemotherapy, occurring in the 3-4 months prior to operation*

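### Cancer treatment given between the paired rectal biopsies is neither excluded, separated nor fully dated, so expression changes it causes could be credited to vitamin D

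*Protocol*

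**What the plan says.** The Study Summary (Design) states that "patients will be identified and recruited from surgical wards or surgical/oncology out-patient clinics", and that "A sample of participants with and without a new or previous diagnosis of colorectal cancer will be included for comparison". The group therefore includes people at the start of their cancer care.

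The sampling interval is set in section 5.6: "Following 12 weeks of Vitamin D supplementation repeat blood (~30mls) and rectal biopsies will be taken". Figure 2 (section 5.11) gives a longer schedule, with biopsies at entry, after 6 weeks without supplementation, and after a further 12 weeks on it.

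The primary outcome in section 3.1 is "the change in expression of genes relevant to colorectal cancer risk in response to vitamin D supplementation". Section 7.2 has "pre and post active treatment gene expression assessed using Illumina HT-12 array" and gives one test: "Statistical comparison of pre- and post-treatment gene expression will be undertaken using the Mann-Whitney U test".

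Cancer treatment appears in three places:

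- Section 5.8 asks for pre-operative treatment and "post-operative treatment including any short or long course of radiotherapy, chemo-radiation, combination chemotherapy, mono-chemotherapy or palliative chemotherapy in participants with colorectal cancer" to be recorded.
- The data collection proforma has a surgery date and tick options for pre- and post-operative treatment. It notes that "Long course is 6 weeks +/- chemotherapy, occurring in the 3-4 months prior to operation", and one post-operative option is that treatment is not yet determined.
- Section 8.2 foresees hospital admissions for operations during the study and leaves them out of adverse event recording.

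Two eligibility rules touch on treatment. Section 4.2 lists recent colonic surgery among the sigmoidoscopy risks, and section 5.4 bars patients who are on treatment trials.

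**The concern.** A pre/post comparison attributes to the intervention whatever else changed systematically between the two samples. For a newly diagnosed patient, cancer treatment is an obvious candidate. An operation, chemotherapy or pelvic radiotherapy could plausibly alter the tissue being sampled. The protocol gives no figure for such an effect, so its existence and size are assumptions here.

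If some pairs span treatment and it moves a gene in a consistent direction, the estimated change is shifted. More participants would not cure this, because the shift stays while the standard error shrinks. It could create an apparent vitamin D response or hide a real one. Section 1.1 offers the interventional design as the answer to reverse causality, so a route by which the disease and its management re-enter the estimate deserves to be closed.

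**Working it through.** **1. Can treatment fall between the biopsies?** The proforma puts long-course radiotherapy at 6 weeks; the supplemented interval is 12 weeks and the longer schedule spans 6 + 12 = 18. A whole course fits inside either. Section 8.2 shows that operations during the study are expected.

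**2. Does a rule remove or mark such pairs?**

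| Provision | What it covers | What it leaves open |
|---|---|---|
| 4.2, recent colonic surgery | Entry, as a sigmoidoscopy risk | Later surgery; all chemotherapy and radiotherapy |
| 5.4, treatment trials | Trial treatment at entry | Routine treatment |
| 4.3, withdrawal | Withdrawal of consent | Treatment during the interval |
| 8.2, adverse events | Excludes events clearly due to the cancer | Cannot serve to find treated pairs |
| Proforma | Surgery date, treatment type | Chemotherapy and radiotherapy dates |

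No provision excludes the pairs, and the form cannot fully classify them afterwards.

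**3. Does the stated comparison cancel the effect?** The single-sample group has no second biopsy. The 6-week lead-in precedes supplementation, so it does not cover the same weeks, and 7.2 makes no use of it.

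**4. Size.** The protocol has no figure for this bias to reproduce. Let *p* be the share of pairs with interval treatment, *g* the mean shift it causes, and *d* the vitamin D effect. Then

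expected mean change = *d* + *p* × *g*, so bias = *p* × *g*.

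From section 7.1: maximum SD 0.42, significance level 0.005, and 18 and 57 as two of its four listed sample sizes, used only as examples. Assumed, not in the protocol: *p* = 10-50%, *g* = 1-2 SD (0.42-0.84 units) in one direction, pre/post correlation 0.5, and *d* = 0.

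- Lowest: 0.10 × 0.42 = 0.042 units (0.1 SD).
- Highest: 0.50 × 0.84 = 0.42 units (1.0 SD).

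Simulated share of false positives per gene at nominal 0.5% (4,000 runs per cell):

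| *p*, *g* | Bias (units) | n=18 Mann-Whitney | n=18 paired t | n=57 Mann-Whitney | n=57 paired t |
|---|---|---|---|---|---|
| 10%, 1 SD | 0.042 | 0.03% | 0.8% | 0.1% | 2% |
| 25%, 1 SD | 0.105 | 0.2% | 2.6% | 1.7% | 12% |
| 25%, 2 SD | 0.21 | 1.3% | 6% | 13% | 47% |
| 50%, 2 SD | 0.42 | 20% | 44% | 92% | 99% |

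The Mann-Whitney test treats the two samples as independent. With positively correlated pairs it is conservative: with no treated pairs it rejected in at most 0.025% of runs. That is why its low-end rates lie below 0.5%. The bias in the estimated change is the same under either test.

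**The case against.** The strongest reply is that analysis sets, sensitivity analyses and subgroup reports belong in a statistical analysis plan, which may exist and is not shown. That stands for part of the matter. The absence from 7.2 of a comparison by cancer status is not a fault, and although a reader might infer that 7.2 pools every participant, it does not say so. The reply does not reach eligibility, biopsy timing, the uncontrolled primary comparison or the dates collected, all of which this protocol sets. A later plan cannot sort pairs by dates that nobody recorded.

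A reader might also infer that the study has no control information at all and that the whole treatment effect must enter the estimate. That is too strong. The lead-in in Figure 2 is a within-person unsupplemented period. Section 5.7, in a garbled sentence, says that people not taking vitamin D have the same assessment as others, whereas the Study Summary offers them a single sampling; those passages need reconciling. Neither source, as described, would cleanly remove treatment effects during supplementation.

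It is tempting, too, to pick one scenario and claim that treatment alone reaches significance. With 30% treated and a shift of 1.5 SD of the differences, the bias is 0.30 × 1.5 = 0.45 SD, seemingly above the 0.39 SD needed by a paired t-test at n=57. But a mixture of treated and untreated pairs widens the SD to √(1 + 0.3 × 0.7 × 1.5²) = 1.21, so the standardised bias is 0.45 / 1.21 = 0.37, below that threshold. The stated test is also not a paired t, and 57 is not a fixed target.

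Finally, much of the recorded treatment may be history in people with a previous cancer. Surgery and, roughly, pre-operative radiotherapy can be placed in time from the proforma. Different treatments need not move a gene the same way. All of this is fair, and it is why the size must be left open.

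**Conclusion.** The pathway is established by the text. New cancer diagnoses are eligible, treatment can fall between biopsies taken 12 or 18 weeks apart, no provision excludes or separates it, its dates are only partly collected, and the single stated primary comparison attributes the change to vitamin D without an untreated group over the same weeks. An expression change caused by interval treatment could therefore be reported as a response to supplementation.

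The size is unknown. The protocol gives neither the number of affected pairs nor any treatment effect. Under the assumed ranges the bias runs from 0.042 to 0.42 units. The false-positive rate at n=57 runs from about 0.1% to 92% with the stated test and from 2% to 99% with a paired t; at n=18 the ranges are about 0.03% to 20% and 0.8% to 44%. These figures rest on shifts in a common direction and a correlation of 0.5. They show what could happen, not what will. The point warrants a change because the remedy is cheap and the missing dates may be hard to recover later.

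**What to change.** - In section 7.2, define the primary paired set as pairs with no surgery, chemotherapy or radiotherapy between the two biopsies being compared. For the 18-week schedule, name which earlier biopsy is the pre-treatment sample.
- Analyse all pairs as a sensitivity analysis with an interval-treatment indicator, and report how many pairs are affected.
- Add start and stop dates for chemotherapy and radiotherapy to the proforma, and update these and the surgery date at the final visit so that every pair can be classified.

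This needs a few lines of analysis text and a few fields on an existing form. It changes nobody's treatment. The cost is a smaller primary set and so some loss of precision, which the all-pairs analysis partly offsets.

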# 1. INTRODUCTION

# 1.1 BACKGROUND & RATIONALE

Colorectal cancer (CRC) is common, with >1 million annual incidence worldwide and is responsible for large numbers of deaths and considerable morbidity. Prevention is a particularly appealing strategy to combat CRC, but there is a paucity of well-founded mechanistic research.

Vitamin D deficiency has recently been implicated as a major risk factor in CRC aetiology in geographical, cohort and case-control studies. The evidence is strong for association with CRC risk, and with cancer death. However, causality has yet to be established and adequately powered randomised clinical trials have never been conducted.

No previous study has investigated the way vitamin D affects gene expression in the bowel tissue itself and no study has used vitamin D shown a reduction in cancer. While the evidence for vitamin D reducing bowel cancer risk is extremely strong, the concept of ‘reverse causality’ (i.e. that cancer reduces vitamin D levels) cannot be completely ruled out without an interventional study such as is proposed here.

This study aims to uncover the mechanisms via which vitamin D affects bowel cancer risk. Using gene expression as an endpoint rather than cancer incidence means that far fewer study participants are required while the study period can be much shorter.

If we are successful in our aims we will demonstrate the mechanism by which vitamin D reduces bowel cancer risk and support the role of vitamin D use as a public health intervention. Our study will support future work which will contribute to the development of targeted chemoprevention involving vitamin D or related drugs in those at an increased risk of bowel cancer due to their genetic make-up. Finally our study could act as a template for the investigation of other ways environmental factors can affect cancer risk.

# 2. STUDY OBJECTIVES

To demonstrate a change in expression of genes in bowel tissue in response to vitamin D and dependent on genotype at known colorectal cancer risk loci

To demonstrate that vitamin D increases serum and tissue (rectal) vitamin D levels and relate these changes to a change in gene expression.

**To demonstrate a correlation between vitamin D levels and gene expression using single sample measurements.**

To support the development of vitamin D as a preventative agent for bowel cancer

# 3. STUDY DESIGN

# 3.1 STUDY OUTCOME MEASURES

PRIMARY OUTCOME – the change in expression of genes relevant to colorectal cancer risk in response to vitamin D supplementation.

SECONDARY OUTCOMES - the genotypic associations with changes in gene expression in response to vitamin D supplementation, the change in serum and tissue vitamin D level after vitamin D supplementation.

# 4. PARTICIPANT ENTRY

# 4.1 INCLUSION CRITERIA

All participants will be aged 16 years or over.

Participants must be resident in the United Kingdom.

# 4.2 EXCLUSION CRITERIA

The inability to provide informed consent.

Under the age of 16 years.

A non-UK resident.

Patients who may be at increased risk from rigid sigmoidoscopy:

- Individuals who are taking anti-coagulation medication.
- Individuals with platelet disease or other bleeding issues.
- Individuals with a history of a significant rectal bleed.
- Suspected or known bowel perforation
- Anal stenosis
- Acute peritonitis
- Colonic necrosis
- Toxic megacolon
- Acute severe diverticulitis
- Diverticular abscess
- Recent colonic surgery
- Anal fissure
- Severe coagulopathy
- Anticoagulant therapy
- Severe thrombocytopenia
- Severe neutropenia

**Patients who may be at increased risk from Vitamin D supplementation would not be included in the intervention arm but could still be included in the single sample arm:**

- Kidney disease
- High levels of calcium in the blood
- Atherosclerosis
- Sarcoidosis
- Histoplasmosis
- Over-active parathyroid gland (hyperparathyroidism)
- Lymphoma
- Currently taking thiazide diuretics, digoxin or other cardiac glycosides
  - Known allergy to nuts ( as peanut oil contained within vitamin D preparations)
  - Female subjects of child bearing age who are not taking effective contraception during the period of the trial

Patients in whom vitamin D levels may be unpredictable

- Individuals already established on supplementary Vitamin D.
- Individuals recently returned to the UK from an overseas holiday.
- Individuals who have recently lived abroad.
- Patients on anti-epileptic medication

Presence of any of the above exclusion criteria will be elicited from relevant patient records including clinical case notes and recent laboratory tests.

# 4.3 WITHDRAWAL CRITERIA

Study participants are free to withdraw from the study at any time without giving reason. Should consent be withdrawn, the participant and all identifiable data or tissue collected will be withdrawn.

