# 8. ADVERSE EVENTS

The Investigator is responsible for the detection and documentation of events meeting the criteria and definitions detailed below.

Full details of contraindications and side effects that have been reported following administration of Vitamin D can be found in the relevant Summary of Product Characteristics (SmPC).

Participants will be instructed to contact their Investigator at any time after consenting to join the trial if any symptoms develop. All adverse events (AE) that occur after joining the trial must be reported in detail in the Case Report Form (CRF) or AE form. In the case of an AE, the Investigator should initiate the appropriate treatment according to their medical judgment. Participants with AEs present at the last visit must be followed up until resolution of the event.

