# 8.2 IDENTIFYING AEs AND SAEs

All AEs and SAEs will be recorded from the time a participant signs the consent form to take part in the study untilthe end of the study.

Participants will be asked about the occurrence of AEs/SAEs at every visit during the study. Open-ended and non-leading verbal questioning of the participant will be used to enquire about AE/SAE occurrence. Participants will also be asked if they have been admitted to hospital, had any accidents, used any new medicines or changed concomitant medication regimens.

AEs and SAEs may also be identified via information from support departments e.g. laboratories*.*

Events clearly related to a known underlying medical condition, in particular colorectal cancer, will not be recorded, including but not limited to admissions for planned or emergency surgery, admissions with bowel obstruction or admissions with rectal bleeding.

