# 8.5 REPORTING REQUIREMENTS

The ACCORD Research Governance & QA Office is responsible for reporting SAEs that are considered to be ‘possibly related’ and ‘unexpected’ to the REC on behalf of the co-sponsors (Edinburgh University and NHS Lothian).

An Annual Safety Report will be submitted, by ACCORD to the REC listing all SARs.

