# 8.6 FOLLOW UP PROCEDURES

After initially recording an AE or recording and reporting an SAE, the Investigator will follow each participant until resolution or death of the participant. Follow up information on an SAE will be reported to the ACCORD office.

AEs still present in participants at the last study visit will be monitored until resolution of the event or until no longer medically indicated.

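### Section 4.3 withdraws all identifiable data with no exception for safety records, so it cannot be applied literally alongside the adverse event duties in section 8

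*Protocol*

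**What the plan says.** Protocol section 4.3 consists of two sentences. The first gives the right to leave: "Study participants are free to withdraw from the study at any time without giving reason". The second gives the consequence: "Should consent be withdrawn, the participant and all identifiable data or tissue collected will be withdrawn". The section names no category of data that is kept, does not define identifiable, and does not say whether it or section 8 prevails.

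The safety sections state these duties:

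- Section 8 (opening text): "All adverse events (AE) that occur after joining the trial must be reported in detail in the Case Report Form (CRF) or AE form". It adds: "Participants with AEs present at the last visit must be followed up until resolution of the event".
- Section 8.2: "All AEs and SAEs will be recorded from the time a participant signs the consent form to take part in the study", running to the end of the study. Its one stated exclusion is for events clearly due to a known underlying condition.
- Section 8.5 (Reporting of SAEs/SARs/SUSARs): SAEs go to the ACCORD office within a day at the latest. Faxed reports and any follow-up information are kept in the Investigator Site File.
- Section 8.5 (Reporting requirements): "An Annual Safety Report will be submitted, by ACCORD to the REC listing all SARs".
- Section 8.6: "the Investigator will follow each participant until resolution or death of the participant". A further sentence lets monitoring of events open at the last visit end when there is no longer a medical reason for it.

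On coding, section 5.6 says: "All samples will be anonymised through use of an identifying number". The data collection proforma carries name, address and date of birth.

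**The concern.** Section 4.3 withdraws data without an exception for safety. Section 8 collects, keeps and follows safety data without an exception for withdrawal. A site handling someone who withdraws after an adverse event therefore has two instructions and no rule for choosing between them, and different sites could reasonably act differently.

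Any resulting loss is unlikely to be random. An adverse reaction or a problem with a biopsy is a plausible reason to withdraw, and no reason has to be given. If the AE entries of such a participant are removed, the event and any sign that harm prompted the departure may both disappear, leaving a safety record that leans towards no harm.

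**Working it through.** The plan gives no figure on this point, so the check sets the sections side by side. Take a participant who is taking capsules, has an AE entered in the CRF that is still open, and then withdraws consent.

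**1. The entry already made.** Sections 8 and 8.2 require it to be recorded. Section 4.3 withdraws it if it is identifiable. Whether the two clash depends on that word.

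**2. What identifiable covers.** Two readings are open.
- Narrow: only data carrying personal details, such as the proforma. Coded AE entries stay, and there is no clash over existing records.
- Wide: anything that can be traced to the person through the study number. The AE entry and the exposure data go, contrary to sections 8 and 8.2.

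Section 5.6 points both ways. It calls samples anonymised, but by means of a number that identifies. It also speaks only of samples; that CRF entries are coded in the same way is an inference. If the adjective in 4.3 governs tissue as well as data, the narrow reading leaves the tissue clause with nothing to act on, because 5.6 already treats every sample as anonymised. The wide reading is therefore a natural one, though not the only one.

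**3. Serious events.** The one-day reporting limit means that a report will often have been sent before a withdrawal, and section 8.5 then requires it to be kept. Read literally, 4.3 and 8.5 still disagree, but the specific retention rule is the better guide. Its wording names faxed reports, while forms may also be handed in or emailed; I take it to cover all three. The annual list comes from ACCORD, which receives these reports, and nothing in 4.3 tells it to discard them. That list is largely protected.

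**4. Non-serious events and exposure.** No retention rule like that in 8.5 covers non-serious AE entries or capsule-exposure data. These are the records mainly exposed.

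**5. The open event.** Sections 8 and 8.6 require follow-up to continue. The limits named are resolution, death, or no further medical reason; withdrawal of consent is not among them. Section 4.3 withdraws the participant. The protocol does not say how the two fit together.

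**6. Scale.** Section 7.1 gives four scenario sizes. One participant as a share of each is:
- 1/5 = 20%
- 1/8 = 12.5%
- 1/18 = 5.6%
- 1/57 = 1.8%

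These sizes are scenarios and not a planned enrolment. The shares show only that in groups this small, one removed AE record can change the reported picture.

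**The case against.** The strongest case on the other side has five parts.

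*The text does not say that safety data are deleted.* This stands. A reader might infer that 4.3 erases the safety record, but it says withdrawn, limits this to identifiable data, and sits beside a retention rule for SAE reports. The documents support a risk of removal, not a statement of it.

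*The right to withdraw ordinarily limits a follow-up duty.* This is fair as custom, and most sites would probably act on it. But 8.6 does name limits and omits this one, and custom does not settle what happens to entries already made.

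*Safety is neither a primary nor a secondary outcome, and no analysis of reaction rates is described.* This also stands, and it limits the importance of the point. The protocol still sets out AE recording and an annual safety report, and these are only as complete as the records behind them.

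*Letting participants withdraw data and tissue is a defensible choice in a genetic biopsy study.* Agreed. The defect is that its effect on safety data has not been reconciled with section 8. The consent pages are not in the text under review, so what participants are told cannot be judged.

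*Stopping capsules is not withdrawing consent.* This is correct. A reader might infer that someone who cannot tolerate the capsules can leave only through 4.3. Nothing says that stopping them triggers 4.3, and the protocol admits people who do not take vitamin D through single sampling. Its silence on stopping after starting does not support the stronger claim.

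**Conclusion.** The point holds in a limited form. For a participant who withdraws consent with a recorded or open event, section 4.3 read literally cannot be reconciled with the recording, retention and follow-up duties in sections 8, 8.2, 8.5 and 8.6. The exposure is mainly non-serious AE and capsule-exposure data, and follow-up of events still open at withdrawal.

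A reader might also infer that the before/after expression comparison is biased by 4.3. It is not a consequence of this clause: that comparison needs a second biopsy, so early leavers are missing from it whatever 4.3 says.

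The direction of any bias, towards no harm, assumes that some withdrawals are related to harm and that a site applies the wide reading of identifiable. Its size cannot be given, because the protocol states no expected number of withdrawals or reactions. The matter merits correction because the change is small and the affected records may not be recoverable; it does not threaten the primary outcome.

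**What to change.** Reconcile section 4.3 with section 8 in four steps.

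1. Say that withdrawal of consent stops further collection of study data, and that identifiable personal data and stored tissue are withdrawn.
2. Say that AE/SAE and capsule-exposure data recorded up to that date are kept in coded form under the study number and reported under section 8. Define identifiable so that its boundary with coded data is clear.
3. State in section 8.6 how the follow-up duty applies once consent is withdrawn.
4. Align the consent form with the revised text, if it does not already say this.

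The cost is a wording change to the protocol and possibly to the consent form. The real downside is for participants: someone who withdraws could no longer have safety data that are already recorded removed.
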